## 10.3 Missing data

Missing data will be handled according to the recommendation by Jakobsen et al. 2017. We anticipate that the proportion of missing values on primary and secondary outcomes other than health-related quality of life and cognitive function will be less than 5%. For health-related quality of life and cognitive function we expect missing data to be less than 15%.

## 10.4 Subgroup analysis

The heterogeneity of the intervention effect on the primary and secondary outcomes will be assessed in subgroups based on baseline characteristics at randomization.

- Mechanical ventilatory support at the time of randomization (defined as invasive or non-invasive mechanical ventilation or nasal high flow treatment [yes/ no]).
- Acute kidney injury at the time of randomization ( $\geq$  KDIGO stage 1 [yes/ no])
- Sex (male/ female)
- Age ( $\geq$  65 years [yes/ no])
- Frailty Clinical frailty scale ( $\leq$  3, 4,  $>$ 4).
- Weight at admission ( $\geq$  median of the intention to treat population [yes/ no])
- Validated infection as suggested by a Linder-Mellhammar score  $\geq$  3 (yes/ no) (Mellhammar 2022)
- IV fluid at time of randomization  $<$  30 ml/kg (yes/ no)

- Plasma Lactate ( $> 4$  mmol/l) (yes / no)

#### 10.4 Exploratory analyses

We will perform an analysis including only centres in which a median difference in total volume of administered fluid between the groups is  $> 3$  L at day 4. We will also perform a subgroup analysis including only centres in which the median difference in cumulative fluid balance is  $> 2$  L at day 4. Because patients staying longer in the ICU will be exposed to the intervention for a longer time we will perform a subgroup analysis of patients staying four days or more in the ICU. Because the amount of glucose may differ between the intervention- and control group we will also perform an analysis of the interaction between the amount of intravenous glucose prior to full enteral nutrition or initiation of parenteral nutrition and treatment effect.

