### 5.2.1 The intervention group

- Maintenance fluids will be discontinued in participants with a positive cumulative fluid balance who are judged not to be dehydrated by the treating physician.
- Glucose may be used at a maximal dose of 1g/kg/day using 20% or more concentrated glucose solutions starting at 72 h after inclusion as nutrition if enteral feeding is not tolerated. Glucose at this concentration or higher may be started earlier in patients at risk of hypoglycaemia (blood glucose <5 mmol/l and trending downwards) and in patients with insulin dependent diabetes if enteral feeding is not tolerated and if mandated by local protocol.
- Intravenous medications will be concentrated according to a trial specific protocol (Appendix D).
- Enteral nutrition will have an energy density of 2 kcal/ml and administered according to local protocols.
- Participants with neutral or negative cumulative fluid balance will receive maintenance fluids and other fluids such that the total dose covers their daily water need (about 1ml/kg/h).
- Intravenous fluid and enteral water will be used to correct electrolyte disturbances as needed.
- Parenteral nutrition will be given according to local protocol.

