### 5.2.2 Usual Care group

- Non-resuscitation fluids will be administered according to local routines.
- Unless the local protocols dictates otherwise, maintenance fluids (enteral water, crystalloids and/or glucose) will be given at 1 ml/kg/h.
- Unless local protocol dictates otherwise, a maximum glucose concentration of 10% will be used.
- Medications will be concentrated according to local protocol.

Site investigators will establish what constitutes usual care in their ICU prior to initiation of the trial. Site investigators will ensure protocol adherence in the two groups through continuous treatment monitoring.

Resuscitation fluids (albumin, blood products, crystalloids given to correct hemodynamic impairment as noted in patient chart or at a rate of  $\geq 5$  ml/kg/h if indication is unclear) will be administered according to local protocol (Finfer 2010). All other care will be according to local routines and not protocolized.

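### Two exploratory analyses, by ICU stay of four days or more and by intravenous glucose given, condition on post-randomisation data and can show effects that do not exist

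*Protocol*

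**What the plan says.** Protocol section 10.4 (Exploratory analyses) reasons that patients with longer stays are exposed to the intervention for longer, and so "we will perform a subgroup analysis of patients staying four days or more in the ICU". It continues: "Because the amount of glucose may differ between the intervention- and control group", there will be an "analysis of the interaction between the amount of intravenous glucose prior to full enteral nutrition or initiation of parenteral nutrition and treatment effect". The same section plans two analyses restricted to centres where the observed between-arm difference in fluid volume or fluid balance at day 4 exceeds a threshold.

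The glucose rules differ by arm:
- **Intervention (section 5.2.1):** "Glucose may be used at a maximal dose of 1g/kg/day using 20% or more concentrated glucose solutions starting at 72 h after inclusion" when enteral feeding is not tolerated. Earlier use is allowed for patients at risk of hypoglycaemia and, under conditions, for insulin-dependent diabetes.
- **Control (section 5.2.2):** unless local protocol differs, "a maximum glucose concentration of 10% will be used". Default maintenance is 1 ml/kg/h, given as enteral water, crystalloid and/or glucose.

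Three other sections bear on the point. Section 3.3 lists ICU days within 90 days as an explorative outcome. The regular subgroups (section 10.4, Subgroup analysis) use baseline characteristics only. Section 10.2 treats secondary and explorative outcome results as hypothesis generating, yet sets a significance threshold of 0.05 for all analyses.

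**The concern.** A treatment comparison within a subgroup is protected by randomisation only if allocation cannot affect membership. ICU stay of four days or more fails that condition. Patients who die or are discharged before day 4 drop out of the subgroup, and the trial is designed to find effects on mortality and on ventilation-free days. If the intervention changes who is still in the ICU on day 4, the two arms of the subgroup contain different kinds of patient.

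The glucose analysis has the same difficulty in another form. The amount given is partly a component of the allocated strategy. It also accumulates over a window that ends at full enteral nutrition or the start of parenteral nutrition, so it depends on recovery and survival. In the intervention arm, glucose is tied to feeding intolerance, hypoglycaemia risk or diabetes; in the control arm it largely follows local routine. The same amount can therefore mark different patients in the two arms, and an interaction need not mean that glucose modifies the effect.

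At stake is a false signal, possibly called significant at 0.05, in the patients described as most exposed.

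**Working it through.** **Base figures.** The plan gives no figure for these analyses. Its design figures (section 10.1.1) serve as the base: 45% control mortality, a 7.5-point reduction, 5% alpha (taken as two-sided) and 90% power. With the pooled formula, n per arm = [1.960·√(2·0.4125·0.5875) + 1.2816·√(0.45·0.55 + 0.375·0.625)]² / 0.075² = (1.3645 + 0.8896)² / 0.005625 ≈ 903.3, so 904 per arm and 1808 in total, as stated. The illustrations use 1850 patients (925 per arm) and 90-day mortality as the outcome; section 10.4 does not name one.

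**1. ICU stay, true mortality effect zero.** Assumptions, not document figures:
- 60% would stay four days or more before early deaths are removed.
- 15% die before day 4, so each 90-day death is early with probability 0.15/0.45 = 1/3.
- One standard-normal severity raises the log-odds of both death and staying by b per SD.
- The intervention lowers the 60% by s points and leaves death unchanged.

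The subgroup is those who stay and have not died early. Each cell rests on 4 million simulated patients and shows the spurious mortality difference (intervention minus control, percentage points), then the false-positive rate at trial size.

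| s | b = 1.0 | b = 1.5 | b = 2.0 |
|---|---|---|---|
| 0 | −0.1; 5% | 0.0; 5% | 0.0; 5% |
| 5 | +0.7; 5.5% | +1.6; 7.4% | +2.1; 9.4% |
| 10 | +1.7; 7.9% | +3.1; 14.1% | +4.4; 23.9% |
| 15 | +2.5; 11.0% | +4.8; 26.4% | +6.7; 45.4% |

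Worked cell (s = 5, b = 2.0): 47.9% and 43.5% are kept, so n = 443 and 402, with mortality 50.5% and 52.6%. SE = √(0.505·0.495/443 + 0.526·0.474/402) = 3.44 points and z = 2.1/3.44 = 0.61. The false-positive rate is 1 − Φ(1.96 − 0.61) + Φ(−1.96 − 0.61) ≈ 9.4%.

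**2. Shift in the timing of deaths only.** Keep 90-day mortality at 45% and let e be the share dying before day 4. Assume 70% of later deaths and 60% of survivors stay four days or more. Subgroup mortality = 0.7(0.45 − e) / [0.7(0.45 − e) + 0.6·0.55].
- e = 0.15: 0.210/0.540 = 38.9%
- e = 0.12: 0.231/0.561 = 41.2% (+2.3 points)
- e = 0.10: 0.245/0.575 = 42.6% (+3.7 points)
- e = 0.18: 0.189/0.519 = 36.4% (−2.5 points)

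If one arm has e = 0.15 and the other a different value, the subgroup shows that difference although 90-day mortality is equal. It can go either way.

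**3. Glucose doses.** Control default maintenance is 24 × 1 = 24 ml/kg/day. If all of it is 5% or 10% glucose, the dose is 24 × 0.05 = 1.2 or 24 × 0.10 = 2.4 g/kg/day. If it is crystalloid or enteral water, the dose is about 0. Control intake may therefore run from about 0 to 2.4 g/kg/day.

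**4. Glucose interaction, true effect zero.** Assumptions: 1850 patients; severity raises the log-odds of death by 1.0 per SD; mean glucose 100 (control) and 40 (intervention) in arbitrary units with noise SD 40; glucose rises by c × 40 units per SD of severity; 400 runs per setting.

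| c control | c intervention | Interaction falsely significant |
|---|---|---|
| 0 | 0 | 6% |
| 0.5 | 0.5 | 6% |
| 0.2 | 0.5 | 62% |
| 0 | 0.5 | 98% |
| 0.2 | 1.0 | 98% |

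A difference in mean glucose between arms does not by itself inflate the test. A different link with severity does.

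**The case against.** The best defence is that little depends on these analyses. They are headed exploratory, the trial's conclusions rest on the primary outcome, and a detailed statistical analysis plan is promised that could add models and caveats. That limits the weight of the point. It does not remove it: the protocol fixes both conditioning variables without caution, departs from its own baseline-only rule for subgroups, and applies the 0.05 threshold to every analysis.

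The second objection is that the size rests on chosen inputs. That stands. The shares staying, the timing of deaths and the links with severity are not in the documents. If the intervention leaves unchanged who stays and survives to day 4, the stay subgroup shows no bias. At a 5-point fall the false-positive rate is only about 6 to 9%.

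Third, a reader might infer from the dosing rules that the arms hardly overlap in glucose, with control at 1.2 to 2.4 g/kg/day against almost none. The documents do not support that. Control maintenance may contain no glucose; the intervention arm has early exceptions and drugs diluted in glucose (Appendix D); and the window can run past 72 h, when up to 1 g/kg/day is allowed.

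Fourth, a reader might take the four-day subgroup to be the only analysis that randomisation does not protect. It is not. The glucose analysis shares the problem, and the two centre-restricted analyses share it in milder form: they select on post-randomisation fluid data, but keep every randomised patient of a selected centre, and randomisation was stratified by site.

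**Conclusion.** The point holds as a possibility of spurious effects, not as a demonstrated bias of known size. Both variables arise after randomisation. For glucose, dependence on arm is written into the treatment rules, and section 10.4 itself expects a difference. For ICU stay, it follows if the intervention has the kind of effect the trial is looking for.

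Under the stated assumptions and no true mortality effect, the four-day subgroup would show about 0.7 to 2.1 points of false difference for a 5-point fall in the share staying, 1.7 to 4.4 for a 10-point fall, and none if who stays is unchanged. The glucose interaction test keeps close to its nominal level when glucose relates to severity equally in both arms, or not at all, and fails badly when the relation differs.

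A reader might infer that the trial's main result is threatened, or that the protocol presents the four-day subgroup as its purest estimate. Neither follows: the primary analysis does not use these variables, and section 10.4 says only that exposure is longer. The change is worth making because it is cheap and because these results could otherwise be reported as significant treatment effects.

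**What to change.** - **ICU stay.** Replace the observed-stay subgroup by a baseline one, such as predicted ICU stay from SAPS-III and ventilatory support, with the prediction rule and cut-off fixed before the allocation code is broken. Use values taken before randomisation only, because the Appendix A baseline window is ±6 h around enrolment.
- **Glucose.** Replace the amount given by a pre-randomisation modifier, such as the site's usual glucose and maintenance routine. Section 5.2.2 already says "Site investigators will establish what constitutes usual care in their ICU prior to initiation of the trial", but Appendix A lists no such variable, so it must be recorded at site level.
- **If the planned analyses are kept.** State that they condition on post-randomisation variables, report them as descriptive and not as randomised treatment-effect estimates, and exempt them from the 0.05 threshold in section 10.2. The centre-restricted analyses should carry a similar caution.

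The cost is protocol and analysis-plan wording plus one site-level variable; SAPS-III and ventilatory support are already collected. Predicted stay separates exposure less sharply than observed stay, and a site routine answers the glucose question only indirectly.

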#### 10.5 Statisticians

Analyses of results will be performed by two independent statisticians.

#### 10.6 Data safety monitoring committee

There will be an independent Data Safety Monitoring Committee (DSMC) which will monitor the trial according to the charter for the DSMC (Appendix B). The DSMC will arrange with an independent statistician to conduct a blinded interim analysis. The DSMC will be able to request unblinding of data if they find it necessary. The DSMC will be provided with data on survival and can initiate an analysis at any time they request. Lan-DeMets group sequential monitoring boundaries will be used to decide if the trial should be stopped (Lan and Demets, 1983).

#### 10.8 Environmental analysis

In addition to climate impacts, other environmental impacts of the intervention will be estimated using life cycle assessment methodology (Hauschild 2018). A separate detailed protocol outlining the boundaries of the climate- and environmental analysis, the impact assessment methodology and statistical analysis plan will be submitted for publication before the last patient is randomized.

## 10.9 Health economic analysis

We will analyse health economic aspects of the intervention. A detailed plan for such an analysis will be published before the last participant is randomized.

## 11. Publication of Data

The analysis process will be performed with the allocation code unbroken and with the trial arms only known as A and B. Two abstracts of the main publication will be prepared before the allocation code is broken, with the different arms interchanged (one assuming arm A is the intervention arm, and the other assuming arm B is the intervention arm). All authors must approve both versions before the code is broken. The final main publication will be submitted to a peer-reviewed international journal. Authorship will be granted using the Vancouver definitions and depending on personal involvement and fulfilment of the authors' respective roles. The author list will include the steering group members, national investigators and additional names. Centres recruiting >30 participants will be entitled to one name, >60 two names, >100 three names, >150 four names, >220 five names in the author list (additional names). After the author list, there will be added: "and the REDUSE-trial group" and a reference to an appendix with all sites, site investigators and the number of participants enrolled. The main publication will report the primary and secondary outcomes. Exploratory outcomes will, due to complexity of reporting be submitted to a peer-reviewed journal in separate manuscripts, as will the studies based on the biobank. Ideas for additional substudies will be presented to the steering group. The steering group will decide which substudies to prioritize. No substudy will be published prior to publication of the main article.

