## 3. Trial hypothesis and outcomes

The objective is to assess the beneficial and harmful effects of a restrictive strategy for administration of non-resuscitation fluids in adult patients with septic shock.

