### 3.3 Explorative outcomes

- Hospital-free days within 90 days of inclusion
- Vasopressor-free days within 90 days of inclusion.
- Renal replacement therapy (RRT)-free days within 90-days of inclusion.
- Major adverse kidney event (MAKE) at 90-days, defined as the composite of mortality at 90 days, initiation of new of renal replacement therapy, or persistent renal dysfunction (defined as a final inpatient creatinine value  $\geq 200\%$  of the baseline value within 90 days)
- Cumulative dose of diuretics during the first 5 days of inclusion, as measured in defined daily doses per the World Health Organization (WHO).
- Glasgow Outcome Scale Extended (GOSE) at 6 months (McMillan 2016).
- European Quality of Life visual 5 dimension-5 level scale (EQ-5D-5L) at 6 months.
- WHO Disability Assessment Schedule (WHODAS) 2.0 (12 item version) total score at 6 months (Üstün 2010).
- Modified Fatigue Impact Scale (MFIS) at 6 months (Téllez 2005).
- All-cause mortality at 12 months.
- Number of days in the ICU within 90 days of inclusion
- Hypoglycaemia (moderate 3.9 - 2.3 mmol/l and severe  $\leq 2.2$  mmol/l) in the ICU
- Hypernatremia ( $> 159$  mmol/L) in the ICU
- Acid base disturbances (hyperchloremic acidosis [ $\text{pH} < 7.15$  and plasma  $\text{Cl}^- > 115$ ], metabolic alkalosis [ $\text{pH} > 7.59$  and  $\text{S-BE} > 9$ ]) in the ICU
- Central venous catheter related complications that could potentially be related to concentrated drugs given in the intervention group (for example, thrombosis, stenosis, malfunction, and infections) in the ICU

For Swedish sites mortality data will be collected from the National board of Health and Welfare.

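### Section 11 keeps four harm-type events out of the main publication without exception, although the objective covers both benefit and harm

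*Protocol*

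**What the plan says.** Section 3 sets a single objective, to "assess the beneficial and harmful effects of a restrictive strategy for administration of non-resuscitation fluids in adult patients with septic shock". Section 11 then fixes what is published where. On the main paper it says: "The main publication will report the primary and secondary outcomes". On the rest it says: "Exploratory outcomes will, due to complexity of reporting be submitted to a peer-reviewed journal in separate manuscripts". Its only rule on order is: "No substudy will be published prior to publication of the main article".

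The explorative list in section 3.3 contains hypoglycaemia (moderate and severe), hypernatraemia, acid-base disturbances, and catheter complications that the entry itself ties to the concentrated drugs of the intervention arm. Section 11 does not single out any of these.

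Section 5.4 requires the author group to approve two conclusions before the code is broken, one for each possible identity of groups A and B. That requirement covers the outcomes in the main manuscript. Section 11 adds two blinded abstracts of the main publication.

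**The concern.** The rule in section 11 sorts outcomes by tier, and section 3.3 places several harms in the lowest tier. Together they send the metabolic and catheter events away from the paper that states the trial's conclusion. Readers of a mortality result would not find in the same report how often these events occurred in each arm.

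There is a second consequence. The A/B procedure protects interpretation from knowledge of allocation, but it reaches only what is in the main manuscript. Nothing in the Protocol requires these four events to be interpreted before unblinding. Nor can outside readers fill the gap quickly, because section 11.1 opens individual data only about one year after the main report.

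**Working it through.** No figure in the Protocol bears on this point, so the check sets the sections side by side.

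1. **Which outcomes go where.** Section 3.1 has one primary outcome, 90-day mortality. Section 3.2 has four secondary outcomes: the complications composite, ventilation-free days, MoCA-BLIND and EQ-VAS. Section 3.3 has fifteen explorative entries. Four of these are the events at issue. The other eleven (15 − 4) are support-free and stay-related day counts, diuretic dose, functional and quality-of-life scales, the 90-day kidney composite and 12-month mortality. Under section 11 all fifteen go to separate manuscripts.

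2. **Whether the main paper captures the four by another route.** The components of the complications composite are cerebral infarction, acute coronary syndrome, intestinal infarction, limb ischaemia and new stage 3 kidney injury. None of the four events is among them. A fatal event would count in mortality but could not be identified there.

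3. **Whether the four belong to the intervention's harm profile.** For catheter complications, section 3.3 makes the link itself. For hypoglycaemia, section 5.2.1 and Appendix C set conditions on when glucose may start, with an exception for patients at risk, and the exploratory analyses in section 10 foresee that the amount of glucose may differ between arms. For hypernatraemia and acid-base disturbances the Protocol states no mechanism. Their standing as safety events rests on the DSMC charter.

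4. **What the DSMC sees.** Appendix B, section 9 lists acid-base disturbances, catheter complications and severe hypoglycaemia. It also lists a sodium event, labelled hyponatraemia but with the threshold above 159 mmol/L that section 3.3 gives for hypernatraemia. I read it as the same event. Moderate hypoglycaemia is not on the charter's list.

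5. **Whether the stated reason fits.** Section 11 cites complexity of reporting. In Appendix A the four are yes/no items, recorded daily on days 1 to 5 and then daily until discharge from a trial ICU or day 90. Reducing each to patients with at least one event is simple.

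6. **Whether the summary already exists.** It does not. Appendix B, section 10 pools the selected exploratory outcomes and the suspected unexpected events into one 0/1 variable, with a second variable for severe hypoglycaemia. A table for each event has to come from the individual eCRF items.

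**The case against.** The strongest reply is that the Protocol placed in the secondary tier the harms it was most concerned about. Section 3.4 reasons that less fluid may reduce intravascular volume and so cause ischaemia and kidney injury, and it cites an association between restrictive fluid and impaired cognition in ARDS. Those outcomes stay in the main paper, together with mortality. This stands. A reader might infer that the main paper carries no harm data, or only the ischaemia and kidney composite, and that the objective goes unanswered. The Protocol does not support that reading.

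A reader might also infer that these harms will be published after the main paper, so that practice could change before they are known. The text does not say so. The rule on order names substudies, and the papers on exploratory outcomes are not called substudies. Companion papers on the same day would comply. The point does not depend on timing, because even simultaneous papers leave the events outside the main report and its blinded conclusions.

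SUSAEs are a further tempting extension. Section 9 has them recorded and reported to the DSMC and is silent on publication. Silence is not exclusion, and the section 11 sentence on exploratory outcomes does not reach them.

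Finally, safety tabulation is commonly left to the statistical analysis plan, which section 10 promises before the last randomisation. That plan can define the table. Here, however, section 11 is not silent. It states a rule, and a plan that put these events in the main paper would depart from it.

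**Conclusion.** The point holds as a minor one. Four of the fifteen explorative entries are harm-type events that the trial's own DSMC monitors (hypoglycaemia only if severe). Section 11 sends them out of the main report, and so out of the A/B conclusions, with no exception. The main paper therefore answers the benefit-and-harm objective incompletely. Collection of the data, monitoring of participants, alpha, power and the primary analysis are all unaffected, and nothing is left unpublished.

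The conclusion assumes that section 11 is followed as written, that the section 5.4 procedure applies only to outcomes in the main manuscript, as its wording indicates, and that the charter's sodium entry is meant as hypernatraemia.

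**What to change.** - **Section 3.3:** put hypoglycaemia, hypernatraemia, acid-base disturbances and catheter complications under a safety-outcomes label, keeping their definitions.
- **Section 11:** state that the main publication tabulates each of the four by arm, as patients with at least one event and a risk difference with confidence interval, and that the blinded conclusions and both abstracts cover them. The other explorative outcomes may stay in separate papers.
- **Clarification only:** say in section 11 that SUSAEs are tabulated by arm in the main publication as well.

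The cost is a few sentences and one more table, with no new data. The table must be built from the individual eCRF items, because the DSMC file pools most of these events. Before it is built, the catheter schedule should be aligned: Table 1 marks days 1, 3 and 5, while Appendix A records catheter complications daily. The table adds no confirmatory test, since section 10.2 already treats everything below the primary outcome as hypothesis generating.
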